#### Secondary analysis

Secondary clinical outcomes will be analysed using logistic regression for binary outcomes and linear regression for continuous outcomes. Results from the analyses will be presented as point estimates with 95% CIs. Baseline scores will be included in the model to increase statistical precision. If more than 5% of data are missing, then imputation techniques may be considered.

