**Figure 1 F1:**
[figure not shown]
Trial design. AE, adverse events; ED, emergency department; EQ-5D-5L, EuroQol 5 Dimensions 5 Levels; GS-PEQ, Generic Short Patient Experiences Questionnaire; NRS, Numerical Rating Scale; PSFS, Patient-Specific Functional Scale; SAE, serious adverse event.

Patients will be invited to participate if they meet the following criteria:

Have an acute (<6 weeks old) simple fracture that can be managed using a removable orthoses (eg, shoulder immobiliser, CAMboot or wrist splint).Aged ≥18 years.Have a condition that is deemed appropriate for virtual management by an orthopaedic doctor.Has access to a phone and will be within New South Wales at the time of consult.Is willing to participate and comply with the study requirements.Have a radiology scan or report to confirm the nature of the injury.

Patients will be excluded if they have:

Complex or significantly displaced fracture, including pathological, open, unstable or spinal fractures requiring a cast or surgical management.Neurovascular concerns.A condition not managed by RPA Hospital Orthopaedics Department.Reported being unable to attend the in-person fracture clinic within the recommended follow-up time.Opted out.

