Health-related quality of life measure assessed using the EuroQol 5 Dimensions 5 Levels (EQ-5D-5L) at baseline and 12 weeks.^16^Patient-reported experience measure assessed using the Generic Short Patient Experiences Questionnaire (GS-PEQ) at 6 weeks.^17^Pain assessed using the 0–10 Numerical Rating Scale at baseline, 6 and 12 weeks.^18^Cost borne by the healthcare service, measured at 12 weeks. We will collect data from the electronic medical records (eMR), SLHD Targeted Activity and Reporting System App Dashboard, and the hospital’s performance, data and finance departments to obtain the healthcare appointment duration, healthcare provider’s hourly rate, any health services utilisation and corresponding cost (including but not limited to outpatient, inpatient, ED, pharmacy, radiology, pathology and primary care), any infrastructure setup and maintenance cost, managerial and administrative overhead.Cost borne by patients, measured through the patient survey designed specifically for this study at 12 weeks.Healthcare utilisation assessed using a survey designed specifically for this study at 12 weeks. The survey will collect the number of other healthcare appointments for management of their injury. We will also ascertain if the patients used any other healthcare services through the patient’s eMR.Medication use assessed using a survey designed specifically for this study to assess the name and dose of prescription or over-the-counter medication for their injury at 6 weeks.Adverse events and serious adverse events assessed using a survey designed specifically for this study at 6 and 12 weeks. We will also collect data from safety reports within the eMR, and the NSW Health Incident Management System.ED representations measured by reviewing the eMRs at 12 weeks. This information may also be reported in the healthcare utilisation survey and the adverse/serious adverse event survey.Number of patients requiring surgery measured by reviewing the eMRs at 12 weeks. This information may also be reported in the healthcare utilisation survey and the adverse/serious adverse event survey.

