### Data monitoring

Given the relatively low-risk nature of the intervention, a data safety and monitoring board will not be used in this study. The study coordinator will provide feedback (at least once per year) to the investigator team, which consists of orthopaedic doctors, senior researchers, hospital executives and a consumer.

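### Surgery and serious adverse events may be too rare for the logistic regression assigned to binary secondary outcomes; add counts and a risk difference with a score-type interval

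*Protocol article*

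**What the plan says.** The Secondary analysis section of the protocol article sets one model family for each type of outcome: "Secondary clinical outcomes will be analysed using logistic regression for binary outcomes and linear regression for continuous outcomes". It then fixes the form of the result: "Results from the analyses will be presented as point estimates with 95% CIs". It adds that "Baseline scores will be included in the model to increase statistical precision".

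The Outcomes section lists these safety-related secondary outcomes:

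- Surgery: "Number of patients requiring surgery measured by reviewing the eMRs at 12 weeks". This is clearly one yes/no value per patient.
- Serious adverse events: "Adverse events and serious adverse events assessed using a survey designed specifically for this study at 6 and 12 weeks", supplemented by safety reports in the medical record and the state incident system. The article does not say whether they are analysed as yes/no per patient or as a count.
- Emergency department representations: "ED representations measured by reviewing the eMRs at 12 weeks". Again, yes/no or count is not stated.

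Three places bear on how often these events may occur. The Eligibility criteria exclude complex or significantly displaced fractures, including "unstable or spinal fractures requiring a cast or surgical management", and a physiotherapist and an orthopaedic doctor screen each referral. The Data monitoring section dispenses with a monitoring board with the words "Given the relatively low-risk nature of the intervention". The Harms section names surgical management of the fracture and emergency department representations among the potential adverse events. No section gives an expected rate for any of them.

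**The concern.** Patients are chosen because their fracture is expected to heal without surgery, so the number who later need it may be very small. With no events in one arm, the maximum-likelihood odds ratio is zero or infinite and its Wald interval is meaningless. With no events in either arm, there is nothing to estimate. The promised point estimate and 95% CI then cannot be delivered by an ordinary fit. Even when the fit converges, an odds ratio from a handful of events is very imprecise and does not show the absolute excess risk.

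At stake is the reading of the safety comparison. A finding that virtual care is non-inferior on function is more useful if readers can see beside it how many more (or fewer) patients per hundred needed surgery or had a serious adverse event.

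**Working it through.** **Arm size.** The Sample size section gives a total of 312, margin 0.7, SD 2.0, α 5%, power 90% and 10% loss. The total reproduces with a one-sided 5% test and no use of the stated correlation:

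- n per arm = 2 × 2.0² × (1.645 + 1.282)² / 0.7² = 139.8, rounded up to 140.
- 140 / 0.9 = 155.6, rounded up to 156 per arm; 2 × 156 = 312.

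Only the arm sizes matter here. 156 per arm suits an outcome read from medical records on everyone randomised, such as surgery. 140 per arm suits an outcome that also depends on survey return, such as serious adverse events.

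**Chance that the fit has no finite estimate.** A maximum-likelihood fit with treatment as a covariate has no finite treatment coefficient when at least one arm has zero events. With a common event rate p and n per arm, one arm has no events with probability q = (1 − p)^n, so

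P(at least one zero arm) = 1 − (1 − q)².

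Example: p = 1%, n = 156 gives q = 0.99^156 = 0.2085, and 1 − (1 − 0.2085)² = 0.3735.

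The documents give no rate, so p is an assumption and a range is shown:

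| Assumed rate, both arms | Expected events, 2 × 156 | n = 156 per arm | n = 140 per arm |
|---|---|---|---|
| 0.25% | 0.8 | 90% | 91% |
| 0.5% | 1.6 | 71% | 75% |
| 1% | 3.1 | 37% | 43% |
| 1.5% | 4.7 | 18% | 23% |
| 2% | 6.2 | 8% | 11% |
| 3% | 9.4 | 1.7% | 2.8% |
| 5% | 15.6 | 0.07% | 0.15% |

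The probability passes 50% only below about 0.8% to 0.9% per arm, and 20% only below about 1.4% to 1.6%. With unequal rates, 1 − (1 − q₁)(1 − q₂) gives 48% (53%) for 0.5% versus 2%, 22% (26%) for 1% versus 3%, and 4% (6%) for 2% versus 5%.

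**What the failure looks like.** A trial fit with 3 versus 0 events of 140 did not converge. The coefficient was about −28 with a standard error of about 670,000, so there is no usable estimate or interval.

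**What the alternatives give (hypothetical counts).**

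- 4/156 versus 0/156: the odds ratio is not finite. The risk difference is 4/156 = 2.6%. The Wilson limits are 1.0% to 6.4% for 4/156 and 0% to 2.4% for 0/156. Newcombe lower limit: 2.56 − √((2.56 − 1.00)² + 2.40²) = −0.3%. Upper limit: 2.56 + √((6.41 − 2.56)² + 0²) = 6.4%.
- 3/140 versus 0/140: a Firth-type fit, which for a two-by-two table equals adding 0.5 to each cell, gives an odds ratio of 7.2 (Wald 95% CI 0.4 to 140). It is finite but very wide.
- 3/156 versus 1/156: the ordinary fit converges, with odds ratio (3/153)/(1/155) = 3.0 and Wald 95% CI about 0.3 to 30.

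**The case against.** The strongest reply is that a condensed article names a model family, and a fallback for sparse events is routinely left to an analysis plan, which is not shown. Its absence is therefore not an error, and that stands. The point rests on the rule the article does state, which suits these outcomes poorly if they are rare.

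Second, the article says only logistic regression. It does not say unpenalised or maximum likelihood, and it does not say odds ratio. Firth and exact fits are forms of logistic regression, so half of the remedy already fits the wording. This also stands, and it makes that part of the fix a clarification.

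Third, a reader might infer three stronger things that the documents do not support:

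- That the stated model will often fail. No rate is given; above about 2% per arm failure is uncommon, and at 3% to 5% it is negligible.
- That eligibility implies few emergency department representations or few adverse events in general. The exclusion of fractures needing a cast or surgery bears on surgery. No criterion limits re-attendance, and the low-risk remark is qualitative.
- That the safety method will be chosen after the data are seen. An analysis plan may already settle it.

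Lastly, preferring an absolute measure can be called a reporting choice, and the intervals above show that a risk difference does not remove imprecision, because the number of events is the limit. That is fair. The gain is an estimate and interval that exist for any count and can be read directly.

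**Conclusion.** The point holds in a limited, conditional form. For surgery, and for serious adverse events if analysed as yes/no, an ordinary maximum-likelihood logistic fit would have no finite treatment estimate in roughly 40% or more of trials if the event rate is about 1% or lower. That falls to about one in ten at 2% and under 3% at 3%. These figures assume equal rates in the two arms and 140 to 156 patients per arm; the rates are assumed, because the article gives none. Low rates are plausible for surgery because of the eligibility criteria and for serious adverse events because of the low-risk setting, but they are not documented.

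These are secondary outcomes, and the non-inferiority conclusion on the Patient-Specific Functional Scale is unaffected. The point is a cheap improvement to the stated analysis.

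**What to change.** In the Secondary analysis section, or in the analysis plan before any comparison by arm is seen, add a rule for surgery, serious adverse events and any other binary safety outcome with few events:

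1. Report the number of patients with the event in each arm, and the risk difference with a score-type 95% CI (Newcombe or Miettinen-Nurminen).
2. If an odds ratio is also wanted, specify Firth-penalised or exact logistic regression.
3. State whether serious adverse events and emergency department representations are analysed as yes/no per patient or as counts, so that it is clear which outcomes the rule covers.

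The cost is wording only; the methods are available in the software named under Statistical methods. The small downside is that the risk difference is not covariate-adjusted. That matters little, because Table 1 shows no baseline value for these outcomes.

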### Sample size

A total sample of 312 participants will provide 90% power to detect a non-inferiority margin of 0.7 points on the 11-point PSFS with a 10% loss to follow-up, an SD of 2.0, α of 5% and a correlation score between baseline and final scores of 0.5 at 12 weeks.^19^ A negative between-group difference of ≤0.7 points will indicate that the VFC clinic is non-inferior to the in-person fracture clinic.

We chose an SD of 2.0 as this is between the mean value of the SD for the PSFS at follow-up in published studies that range from 1.7,^20^ 2.1^21^ and 2.2.^13^ The minimal important difference (MID) for the PSFS ranges from 1.3 (small change) to 2.7 (large change).^21 22^ Guidelines suggest using a non-inferiority margin of 50% (or less preferably) of the treatment effect of standard care versus placebo.^23^ Thus, we chose a between-group non-inferiority margin of 0.7 (50% of the MID of 1.3).

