### Statistical methods

An intention-to-treat analysis will be implemented after the database is cleaned and locked. Separate analyses will be conducted on each outcome. Descriptive statistics will be used for patient demographics and clinical characteristics. Categorical variables will be described with frequencies (%), and continuous variables will be described with means and SD. Data will be analysed using STATA V.14 statistical software (StataCorp) or R V.4.2.1 (R Foundation for Statistical Computing, Vienna, Austria. https://www.R-project.org/).

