### Primary analysis

Non-inferiority trials assess whether an intervention outcome is not clinically worse than a control. The PSFS score at 12 weeks post-randomisation is the primary outcome in this study and we have prospectively defined a non-inferiority margin (ΔT) of −0.7 points, which is the maximum difference we are prepared to tolerate and still consider virtual care not to be clinically inferior to in-person care. The null hypothesis is, therefore, that a difference of greater than ΔT exists in favour of in-person care (H0: Δ ≤−ΔT). This will be assessed by creating a 95% CI, which should be entirely above the non-inferiority margin for the intervention to be declared non-inferior. The PSFS score will be compared between treatment groups as the dependent variable in a generalised linear regression model for the primary analysis adjusting for baseline PSFS variables. The treatment difference will be based on the estimate of adjusted means and 95% CIs.

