#### Cost-effectiveness analysis

The economic evaluation will estimate the difference in the cost of resource inputs used by participants in the two arms of the trial, allowing comparisons to be made between the two models of care.

We will conduct a cost-effectiveness analysis to estimate the incremental-effectiveness ratios (ICERs) defined as: [cost of the virtual care−cost of in-person practice]/[effectiveness of the virtual care−effectiveness of in-person practice]. The effectiveness outcomes include PSFS, ED visit, rehospitalisation and quality-adjusted life-years (QALYs). Costs for resource inputs will largely be derived from available local and national sources and estimated in line with best practice. Primary research using established accounting methods may also be required to estimate unit costs. Costs will be standardised to current prices where possible. The EQ-5D-5L outcomes will be used to generate QALYs, and the responses will be compared with the national Australian value set for the EQ-5D-5L.^16^ Multiple imputation methods will be used to impute missing data and avoid biases associated with complete-case analysis.

To estimate the uncertainty of ICERs, bootstrapping will be used to resample corresponding costs and effectiveness that will be observed in RECITAL, and the distribution of ICERs calculated from all resamples will be plotted on a cost-effectiveness plane. Subgroup analysis will be carried out to assess the equity impact of the interventions. One-way sensitivity analysis will be conducted around key cost variables. A cost-effectiveness acceptability curve will be plotted, which will provide information about the probability that an intervention is cost-effective, given the level of a decision maker’s willingness to pay for each additional effectiveness outcome gained. The economic assessment method will adhere to the Consolidated Health Economic Evaluation Reporting Standards 2022.^24 25^

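### The plan fixes no missing-data method for the primary 12-week PSFS: its only clinical rule is optional, has a trigger the planned loss already exceeds, and leaves the 6-week PSFS unused

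*Protocol article*

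**What the plan says.** The protocol article, under Statistical methods, labels the analysis: "An intention-to-treat analysis will be implemented after the database is cleaned and locked". Under Primary analysis, 12-week PSFS is the dependent variable "in a generalised linear regression model for the primary analysis adjusting for baseline PSFS variables", and the 95% CI for the adjusted difference must lie above −0.7. That section says nothing about participants without a 12-week score.

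The only missing-data sentence for clinical outcomes stands under Secondary analysis: "If more than 5% of data are missing, then imputation techniques may be considered". The Sample size section arrives at 312 "with a 10% loss to follow-up".

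The Cost-effectiveness analysis section, which counts PSFS among its effectiveness outcomes, is firm: "Multiple imputation methods will be used to impute missing data and avoid biases associated with complete-case analysis".

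Table 1 shows PSFS at baseline, 6 weeks and 12 weeks. The list of secondary measures that follows the table does not include the 6-week PSFS, and neither clinical analysis section assigns it a role.

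**The concern.** A regression of a single follow-up score on arm and baseline takes nothing from a participant whose follow-up score is missing. Unless the optional imputation is taken up, the analysis labelled intention-to-treat rests on completers. The rule leaves open whether to impute, by what method, and whether the primary outcome is covered at all. Those choices can then be made once the extent of missingness is known. Because the planned loss is twice the trigger, the choice is likely to arise.

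The result turns on whether a confidence limit clears −0.7, so a shift of one or two tenths of a point can change the conclusion. The document recognises the problem for the economic evaluation and settles it there, so the trial could report an imputed PSFS difference in one place and a completers-only one in the other. The 6-week PSFS, which could inform missing 12-week scores at no extra data cost, is not put to that use.

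**Working it through.** **The plan's own figure.** "A total sample of 312 participants will provide 90% power to detect a non-inferiority margin of 0.7 points on the 11-point PSFS", with SD 2.0, 10% loss, α 5% and "a correlation score between baseline and final scores of 0.5 at 12 weeks". With one-sided α of 5% and no variance reduction from baseline:

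- n per arm = 2 × 2.0² × (1.645 + 1.282)² / 0.7² ≈ 139.8, so 140.
- Inflated for loss: 140 / 0.9 ≈ 155.6, so 156 per arm, or 312 in total. The figure reproduces.

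**Planned loss against the trigger.** 10% of 312 is about 31 people; 5% of 312 is about 16. The plan expects twice the trigger.

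**Power is not the issue.** The baseline-adjusted regression on 140 completers per arm has SE = 2.0 × √(1 − 0.5²) × √(2/140) = 0.207. For a two-sided 95% CI and a true difference of zero, power = Φ(0.7/0.207 − 1.96) ≈ 92%. What remains at stake is bias.

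**Size of a possible bias.** Assume a share m of the virtual arm is missing and those people score d points below completers beyond what baseline explains, with no such gap in control. The mean of the whole virtual arm is then m × d below the completers' mean, so the completers-only difference is too favourable by m × d. At a true difference of −0.7, the chance of declaring non-inferiority is Φ(m × d / 0.207 − 1.96). With m = 0.10 and an assumed range for d:

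| d (points) | bias (points) | share of margin | one-sided error at the margin |
|---|---|---|---|
| 0 | 0 | 0% | 2.5% |
| 1 | 0.10 | 14% | 7.0% |
| 1.3 | 0.13 | 19% | 9.1% |
| 2 | 0.20 | 29% | 16.0% |

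With equal m and d in both arms the two shifts cancel: 0.10 × d − 0.10 × d = 0. With the gap in control only, the sign reverses: for d = 1 the bias is −0.10 and the error falls to Φ(−0.10/0.207 − 1.96) ≈ 0.7%.

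**Simulation.** There were 4,000 runs per scenario, with 156 per arm, a true difference of −0.7 and 10% missing per arm. Loss depended on the 6-week PSFS. The correlation of baseline with each follow-up was 0.5. The correlation between 6 and 12 weeks was assumed to be 0.7, since the documents give none. The 6-week score was taken as observed for everyone.

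| What drives loss | completers-only bias | one-sided error |
|---|---|---|
| Poor 6-week score, virtual arm only (two strengths) | +0.09, +0.13 | 5.8%, 9.2% |
| Poor score in virtual, good score in control | +0.17 | 12.1% |
| Poor score, same mechanism in both arms | about 0 | 2.7% |
| Poor score, control only | −0.08 | 0.9% |

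In every scenario, an estimate that also used the 6-week score had bias within 0.01 of zero.

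**The case against.** The strongest reply is that this is a condensed article and that imputation models, intermediate visits and sensitivity analyses belong in an SAP that is not shown. That stands for the detail. It does not cover what the article does state: a specific primary model and a discretionary rule, beside a firm commitment for the economic evaluation.

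A reader might infer that the protocol discards everyone without a 12-week score. It does not say so. That is how the stated model behaves by default, and the 5% sentence leaves imputation open.

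A reader might also infer that the missing data will favour non-inferiority. The documents do not support a direction. Both arms receive the same survey links, reminders and completion payment. Participants and clinicians are unblinded, and clinicians may prompt survey completion at reviews whose pattern differs by arm. So an equal mechanism cannot be assumed, but neither can loss of poor responders from the virtual arm alone.

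Three further points stand:

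- Regression at one time point is a conventional primary analysis, and it is unbiased if loss depends only on arm and baseline.
- A raw gap between missing and observed participants overstates the bias, because baseline adjustment removes part of it. For this reason d above is defined as the gap beyond baseline.
- A mixed model is not the only remedy, and no method based on observed scores corrects loss that depends on unseen 12-week function.

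Finally, the article promises separate analyses of each outcome and does not limit PSFS in the economic evaluation to 12 weeks. It would therefore be too strong to say that the 6-week score will go unused everywhere. It has no described role in the clinical analyses.

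**Conclusion.** The point holds as a weakness in what the plan fixes, and it should be corrected. The primary analysis has no committed missing-data method. The only clinical rule is optional, of unclear scope, and has a trigger at half the planned loss. The 6-week PSFS is collected without a described clinical use.

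The consequence is a possible bias whose direction is not known. The 0.1 to 0.2 points, and the error of about 7% to 16%, rest on assumptions: 10% missing in the virtual arm, a gap of 1 to 2 points beyond baseline, no such gap in control, and a completers-only analysis. Other equally admissible assumptions give no bias or a bias against non-inferiority. The figures show that the choice of method can matter on the scale of the margin; they do not predict the result.

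**What to change.** Replace the optional 5% rule with a prespecified primary method that includes all randomised participants and uses PSFS at baseline, 6 weeks and 12 weeks. Either of two routes serves:

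- a repeated-measures mixed model with arm-by-visit effects and an unstructured covariance; or
- multiple imputation by arm that includes the 6-week score, followed by the regression already stated.

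In both, the 12-week contrast and its 95% CI remain the primary estimate, judged against −0.7. State explicitly that the rule covers the primary outcome.

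Because either route corrects only loss explained by observed scores, add a tipping-point sensitivity analysis. This shifts imputed 12-week values in the virtual arm downward until non-inferiority is lost, and reports how large that shift must be.

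The cost is plan wording, some extra programming, and a covariance structure or imputation model to specify. No new data are needed.
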